### SHI claims data

2.3

#### SHI study population

2.3.1

The SHI population for EvaClosure is selected from the data pool of a German statutory health insurance fund that comprises over 3 million insured persons. EvaClosure uses data from the years 2015 to 2021. Patients are selected if they
are 18 years or older, andhave a diagnosis code (of the 10th revision of the International Statistical Classification of Diseases and Related Health Problems; ICD-10) for AF documented in at least two different quarters during the baseline period (I48.0, I48.1, I48.2, I48.9)Patients are excluded from the sample in case of
discontinuous data coverage (e.g., due to interrupted insurance periods or change of health insurance fund)an absolute contraindication for ASA (an ICD-10 code for gastric or duodenal ulcers (K25.- or K26.-) or a prescription for methotrexate [Codes within the Anatomical Therapeutic Chemical Classification System (ATC): L01BA01 or L04AX03])previous heart transplant (code within the German Operation and Procedure Classification System; OPS: 5–375)malignant neoplasm of the heart, mediastinum, and pleura (ICD: C38.-) orpregnancy, birth, or postpartum diagnosis in the baseline period (ICD: O–.—)Patients are assigned to the high-risk group if in the baseline period they additionally have the following characteristics:
CHA_2_DS_2_VASc-Score ≥ 2, andhigh risk for bleeding, i.e., if at least one of the following criteria are met:
○HAS-BLED value of ≥ 3, or○an ICD-10 code for other non-traumatic intracranial hemorrhage (I62.-), or○gastrointestinal bleeding (K92.2), or○hematuria (R31), or○bleeding from the respiratory tract (R04.-), or○chronic kidney disease (N18.4)From the high-risk patients, the LAAC intervention group is selected using the following inclusion criteria:
Diagnosis-related group (DRG): F95A (interventional septal occlusion, age < 18 years, or atrial appendage occlusion) andOPS code 8-837.s0 (since 2016) or 8-837.s (before 2016)The control group (best medical care group) is also selected from the group of high-risk patients, defined by the following criteria:
no LAAC [DRG: F95A; OPS code 8-837.s0 (since 2016) or 8-837.s (before 2016)] procedure documented andtreatment with best medical care (NOACs (dabigatran (ATC code B01AE07), rivaroxaban (ATC code B01AF01), apixaban (ATC code B01AF02), edoxaban (ATC code B01AF03)) or VKA [phenprocoumon (ATC code B01AA04), and warfarin (ATC Code B01AA03)]For both groups, an additional exclusion criterion according to the CLOSURE-AF trial of a severe renal failure (ICD N18.5) or current requirement for dialysis (ICD Z49.1, Z49.2 in the quarter of inclusion) is applied (23).

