The CLOSURE-AF-DZHK16 study addresses this research gap. CLOSURE-AF is a prospective, randomized clinical trial involving 42 study centers in Germany^1^ that analyzes the clinical benefit of LAAC in patients with non-valvular AF (NVAF) at high risk of stroke and bleeding (high-risk group)^2^ compared with best physician–directed medical care (including anticoagulation, when tolerated). Patient enrollment began in February 2018, with a study completion date in November 2024. Subjects were randomized 1:1 in the intervention and control group, receiving either catheter-interventional LAAC with a CE-certified LAA occluder (e.g., Watchman™, Amplatzer Amulet) or physician-directed best medical care [NOACs or vitamin K antagonists (VKA), antiplatelet therapy, no antithrombotic/antiplatelet therapy in case of contraindications] chosen at the discretion of the treating physician (23).

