#### EvaClosure study population

2.2.1

The EvaClosure population comprises a subgroup of the CLOSURE-AF trial participants who consented to participate in the health economic evaluation (=EvaClosure study). Thus, the EvaClosure population includes both newly recruited patients and study participants who had already been enrolled in the CLOSURE-AF trial (see the section “trial data collection” for further details).

Patients enrolled in the CLOSURE-AF study do not have to meet any further criteria (apart from giving consent) to participate in the EvaClosure substudy. The eligibility criteria for CLOSURE-AF have been described elsewhere in detail (23); the trial includes patients 18 years or older with documented AF (paroxysmal, persistent, or permanent) and with high risk of bleeding or stroke. High risk of bleeding and stroke is determined by the CHA_2_DS_2_VASc and HAS-BLED scores as well as other characteristics [see (37, 38)]. Moreover, patients must be suitable candidates for catheter-interventional atrial appendage closure. Only those patients with an absolute contraindication to ASA and other antiplatelet drugs such as P2Y12-inhibitors like clopidogrel or with other comorbidities requiring long-term (N)OAC treatment were excluded from the study. Patients in the control group will be treated at the discretion of their local physician according to recommendations based on their specific bleeding risk. Patients will receive one of four approved NOAC treatments in different doses, including the relevant dose-reduction criteria: dabigatran, rivaroxaban, apixaban, or edoxaban. Table 1 summarizes the approved (N)OACs and doses. In case of contraindications to NOACs, patients may be either treated with vitamin-K antagonists (warfarin, phenprocoumon) and antiplatelet agents or there will be no stroke preventive treatment.

**Table 1 T1:** (N)OACs and approved/studied doses across indications.

(N)OACs	Higher dose	Lower dose
Dabigatran	150 mg BID (CrCl >30 mL/min)	110 mg BID [Age >80, Interacting drugs (e.g., verapamil), CrCl 15–30 mL/min]
Rivaroxaban	20 mg/d (CrCl >50 mL/min)	15 mg/d (CrCl 15-50 mL/min)
Apixaban	5 mg BID	2.5 mg BID (if two of the following present: age >80, weight <60 kg, serum creatinine >1.5 mg/dL)
Edoxaban	60 mg/d	30 mg/d (weight <60 kg, CrCl 15-50 mL/min)

BID = twice daily; CrCl, creatinine clearance.

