### Outcome measures and analyses

2.4

The EvaClosure study design consists of four modules that build on one another (see Table 2). For module A1, a cost-of-illness study assesses direct and indirect costs associated with a high risk of stroke and bleeding in patients with AF. Focusing on the high-risk group only, module A2 compares direct and indirect costs associated with LAAC treatment to best medical care. Module B1 quantifies the utility effect of LAAC in terms of QALYs gained compared with standard of care via data of the EvaClosure study population. The subsequent module B2, on the other hand, combines SHI claims data and data from the EvaClosure study population as well as CLOSURE-AF trial results to conduct a cost–utility analysis.

**Table 2 T2:** Overview study modules, design, and outcome measures.

Module	Main Objectives	Study population	Design	Time frame	Costs/Outcomes
A1	To assess cost of illness to high-risk of stroke and bleeding in patients with AF	SHI study population, divided into the high-risk AF group and the AF group without high risk	Longitudinal cohort study, retrospective (difference-in-differences)	2015–2021; 1 year before and 4 years after inclusion per individual	direct and indirect costs
A2	To assess direct and indirect costs of LAAC intervention vs. best available medical care in high-risk patients with AF	EvaClosure study population: high-risk AF patients divided into intervention and control groups as per the CLOSURE-AF protocol.	Longitudinal cohort study, prospective (difference-in-differences)	2018–2025; enrollment starting in 01/2021 with a follow-up of up to 24 months	Direct and indirect costs
		SHI study population: the high-risk AF group divided into intervention and control groups as close as possible to the CLOSURE-AF protocol	Longitudinal cohort study, retrospective (difference-in-differences)	2015–2021; 1 year before and 4 years after inclusion per individual	
B1	To assess the utility effect of LAAC compared with best medical care	EvaClosure study population: high-risk AF patients divided into intervention and control groups as per the CLOSURE-AF protocol	Longitudinal cohort study, prospective	2018–2025; CLOSURE-AF enrollment starting in 03/2018; obtaining informed consent for prospective and retrospective participation in EvaClosure started in 01/2021, patient individual follow-up of up to 24 months	Health-related quality of life, QALYs

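### The claims cohorts for the LAAC comparison drop two CLOSURE-AF eligibility restrictions, so an unknown share of the anticoagulated controls may be trial-ineligible

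*Protocol article*

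**What the plan says.** **Trial side.** Section 1.1 (Background) says that CLOSURE-AF "analyzes the clinical benefit of LAAC in patients with non-valvular AF (NVAF) at high risk of stroke and bleeding". Section 2.2.1 (EvaClosure study population) adds that patients "with other comorbidities requiring long-term (N)OAC treatment were excluded from the study", in the same sentence that excludes an absolute contraindication to ASA and other antiplatelet drugs.

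**Claims side.** Section 2.3.1 (SHI study population) takes adults with a code "for AF documented in at least two different quarters during the baseline period (I48.0, I48.1, I48.2, I48.9"). Its exclusions are given code by code:

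- gaps in insurance coverage;
- "an absolute contraindication for ASA (an ICD-10 code for gastric or duodenal ulcers (K25.- or K26.-) or a prescription for methotrexate" (ATC codes follow);
- "previous heart transplant (code within the German Operation and Procedure Classification System; OPS: 5–375");
- malignant neoplasm C38;
- pregnancy-related diagnoses;
- for both treatment groups, severe renal failure or dialysis, which the article attributes to the trial's criteria.

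Controls must have no LAAC procedure and must be treated with a listed NOAC or VKA.

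**Stated aim.** Table 2, module A2, describes the claims population as "the high-risk AF group divided into intervention and control groups as close as possible to the CLOSURE-AF protocol".

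**Use.** Section 2.4.2 draws costs from these groups after matching on age, gender, comorbidity, the two risk scores and medication class. Section 2.4.4 takes transition risks for the Markov model from the matched claims groups.

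**The concern.** Two restrictions that define who could be randomised have no counterpart in the claims rules. A claims patient with AF and valve disease, or with a separate reason for permanent anticoagulation, meets every written criterion but falls outside the trial population as the article describes it.

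The omission need not affect both groups equally. The AF criteria are common to both, but controls are then selected on anticoagulant use. That favours patients who take the drug for another reason, while someone who must stay anticoagulated has less reason to receive LAAC.

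What is at stake is the coherence of the cost-utility result. The QALYs come from a trial sample that excludes such patients, whereas the claims-based costs and event risks may include them. The two parts of the ICER would then describe somewhat different populations, and the claims contrast between LAAC and medical care could partly reflect the indication for anticoagulation.

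**Working it through.** **1. Criteria side by side**

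| Trial restriction | Claims counterpart (2.3.1) |
|---|---|
| Non-valvular AF (1.1) | None: any of four I48 codes, no valve code |
| No ASA/antiplatelet contraindication (2.2.1) | Ulcer codes or methotrexate |
| No other condition requiring long-term (N)OAC (2.2.1) | None |
| Renal exclusion (cited in 2.3.1 as a trial criterion) | N18.5 or dialysis codes |

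One half of the exclusion sentence in 2.2.1 has been turned into codes and the other half has not. Since the section gives the operational code list, applying it as written admits these patients.

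**2. Does requiring an anticoagulant enrich the control group?** The documents give no figures, so every input here is an assumption. Let q be the share of high-risk claims patients with a trial-ineligible indication, and u1 and u0 the anticoagulant uptake with and without it. Before matching, the ineligible share of controls is

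s = q·u1 / (q·u1 + (1 − q)·u0).

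Example: q = 5%, u1 = 0.95, u0 = 0.70 gives 0.0475 / (0.0475 + 0.665) = 6.7%.

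| q | u1/u0 = 0.90/0.90 | 0.95/0.70 | 0.95/0.50 |
|---|---|---|---|
| 1% | 1.0% | 1.4% | 1.9% |
| 5% | 5.0% | 6.7% | 9.1% |
| 10% | 10.0% | 13.1% | 17.4% |
| 20% | 20.0% | 25.3% | 32.2% |

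Whenever u1 exceeds u0, s exceeds q. The mechanism holds, but the size is open.

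**3. What difference-in-differences removes.** Suppose ineligible controls cost d_pre more than eligible ones before the index quarter and d_post more after it. The before-after change in the control mean is then off by s·(d_post − d_pre). A constant excess cancels; only a changing one remains. The documents do not say which applies.

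**4. What it does not touch.** Event risks for the Markov model are levels, not changes. If r is the ratio of an ineligible to an eligible patient's event risk, the control risk shifts by s·(r − 1) in relative terms. With assumed values:

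- s = 5%: r = 1.1 gives 0.05 × 0.1 = +0.5%; r = 2.0 gives 0.05 × 1.0 = +5%; r = 0.8 gives 0.05 × (−0.2) = −1%.
- s = 17%: r = 1.1 gives +1.7%; r = 2.0 gives +17%; r = 0.8 gives −3.4%.

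The sign follows r, which the documents do not give. Any ineligible patients in the LAAC group would offset part of the shift in the contrast.

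**The case against.** The strongest reply is that the plan has several safeguards, and that the stated aim is closeness to the trial, not identity with it.

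- **Matching.** The claims sample is matched to trial patients, who already satisfy both restrictions. Section 2.1 lists medical history and comorbidities among the trial data used, and 2.4.2 adds a check of the match against medication, events and comorbidities. Matching on medication class could remove an excess of VKA users. This stands in part. But the content of the comorbidity variable is not specified, and neither valve status nor indication for anticoagulation is named, so one cannot assume that the match separates these patients.
- **Cost estimator.** Sections 2.4.2 and 2.4.4 and Table 2 name difference-in-differences. A constant cost gap would therefore largely disappear, so multiplying an assumed cost ratio by an assumed annual cost does not give the bias in A2.
- **Markov risks.** Section 2.4.4 starts from a published model and adjusts the final one with clinical study results; section 2.5 plans a re-parameterisation with trial results. This may correct some event risks. It does not change who is in the claims cost cohort, and the article does not say which claims-based parameters would be replaced.
- **Acknowledged differences.** Section 3 recognises that variable definitions differ between sources. That is a general caution and does not name this mismatch.
- **Full trial criteria not shown.** The article refers to another publication for them, so exactly which conditions count cannot be read here. That limits the detail of the remedy, not the finding that no counterpart is listed.

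A reader might infer that the control group consists largely of ineligible patients, that LAAC is thereby made to look cheaper and more effective, and that a euro amount can be attached. The documents support none of these: they give no share, cost ratio or risk ratio.

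**Conclusion.** The mismatch is real on the text. Two restrictions stated for CLOSURE-AF are absent from a code-level list that carries over other trial exclusions, against the plan's own aim in Table 2. Selecting controls on anticoagulant use allows trial-ineligible patients to enter that group preferentially, provided their uptake is higher than that of other high-risk patients. The planned matching and trial-based adjustment may reduce the effect but do not reliably remove it.

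The proportion affected, the size of any bias and its direction are unknown. The figures above only illustrate the mechanism under assumed inputs and apply before matching. This is a point that should be fixed, held with moderate confidence; it does not show that the planned result is invalid.

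**What to change.** For both claims groups in modules A2 and B2:

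1. Add baseline exclusions, by diagnosis and procedure codes, for valvular AF and for other indications for long-term anticoagulation. The list should mirror the full trial criteria and be agreed with the CLOSURE-AF investigators, who already helped to select codes for module A1 (section 2.4.1).
2. Report how many patients the new exclusions remove in the LAAC group and in the control group. This replaces the assumed shares above with a count.
3. Repeat the A2 cost comparison and the claims-based transition risks without the exclusions as a sensitivity analysis.

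If the sponsor prefers to keep the present criteria, sections 1.1 and 2.2.1 should be reconciled with 2.3.1, with the omission justified and tested in the same way.

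The cost is one code list and a rerun of cohort selection and the dependent analyses. Section 2.3.2 shows that ICD-10 diagnoses and OPS procedures are in the extract. There are two drawbacks. There will be fewer claims controls, though the fund covers over 3 million insured persons. And since only one baseline year is guaranteed, older valve surgery would have to be found mainly through diagnosis codes, so some ineligible patients will remain.

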### Objective

1.2

In parallel to the CLOSURE-AF study, EvaClosure^3^ adds to previous evidence by comparing the LAAC procedure with best medical therapy prescribed by practitioners in a high-risk patient pool (including patients with potential contraindications to NOACs), evaluating its real-world health economic impact. EvaClosure uses both primary clinical study data and real-world German SHI claims data to analyze LAAC cost-effectiveness in comparison with currently available pharmaceutical alternatives. The incremental cost-effectiveness ratio (ICER) of the LAAC treatment is calculated using data from the different databases. A Markov model is used to further evaluate the health economic effects in a lifetime horizon. The model is parameterized with health-related quality-of-life effects (aggregated to QALYs) in the different study arms of the CLOSURE-AF study as well as direct and indirect costs estimated from SHI claims data, supplemented with patient-reported healthcare resource use and data from the literature.

In summary, EvaClosure aims to
assess resource utilization and medical costs associated with a high risk of stroke and bleeding in patients with AFassess direct and indirect costs in high-risk AF patients and of LAAC intervention vs. best medical careassess the utility effects (QALYs) of LAAC compared with best medical care in high-risk AF patientsevaluate the cost-effectiveness of the LAAC intervention compared with best medical care based on the ICER two and five years after intervention as well as in a life-time-horizon from the perspectives of both SHI and society.

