#### B2: health economic evaluation of LAAC

2.4.4

In module B2, a cost–utility analysis compares LAAC with best medical care. Based on the results of modules A2 and B1, the ICER up to five years after intervention is calculated, with QALYs serving as the main effect measure. The ICER determines the costs to SHI (perspective 1) as well as society (perspective 2) for an additional QALY gained. Depending on the underlying perspective, it will be calculated from direct and indirect costs in SHI claims data, supplemented by an analysis of FIMA data from EvaClosure study patients and QALYs derived from EvaClosure study patients as described in the previous section.

A Markov model adapted from the literature (46) will be employed to capture a lifetime horizon to assess long-term effects on costs and health-related quality of life. The transitions between different health states are linked by probabilities, and the Markov property assumes that the transition probabilities result exclusively from the current state (not from history). The parameters of the initial model (46) will be fine-tuned by SHI claims data estimates to capture probabilities for patients with high-risk AF, with risk estimates evaluated among matched populations of both treatment and control claims data groups. Further relevant parameters depending on the underlying Markov state (costs, utilities) will be derived from SHI claims data analyses and the EvaClosure primary data. Parameters that cannot be sufficiently quantified by one of these data sources may be extracted from the literature or health states may be coarsened. After completion of the CLOSURE-AF trial, clinical study results and comorbidity data of EvaClosure-enrolled patients will be used to adjust the final model.

To compare costs and health effects in different years, future costs and benefits will be discounted by an annual discount rate of 3% for SHI expenditures, indirect costs, and QALYs (47). The influence on the results will be systematically addressed in sensitivity analyses as described in the next section.

Figure 1 provides an overview of the study design, the main analyses, the two corresponding data sources, and matching criteria to ensure comparability of the SHI- and trial samples.

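### The two- and five-year ICER appears to combine a claims cost difference by procedure received with a trial QALY difference by randomised arm, and nothing in the plan aligns the two

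*Protocol article*

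**What the plan says.** **Trial side.** Section 1.1 reports that "Subjects were randomized 1:1 in the intervention and control group". Section 1.2 says the model is parameterised with "health-related quality-of-life effects (aggregated to QALYs) in the different study arms of the CLOSURE-AF study". Table 2 (section 2.4) describes the B1 population as "high-risk AF patients divided into intervention and control groups as per the CLOSURE-AF protocol".

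**Claims side.** Section 2.3.1 states: "From the high-risk patients, the LAAC intervention group is selected using the following inclusion criteria". The first criterion is "Diagnosis-related group (DRG): F95A (interventional septal occlusion, age < 18 years, or atrial appendage occlusion"), and an OPS code for the procedure is also required. Controls come from the same high-risk pool. They must have no LAAC documented and must be treated with a NOAC or a VKA. Table 2 calls this "the high-risk AF group divided into intervention and control groups as close as possible to the CLOSURE-AF protocol". Section 2.4.2 takes the two- and five-year healthcare cost of LAAC as the difference between these claims groups.

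**Combination.** Section 2.4.4 says: "Based on the results of modules A2 and B1, the ICER up to five years after intervention is calculated". Costs come from SHI claims supplemented by FIMA data from trial patients; QALYs come from trial patients.

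**The concern.** A randomised LAAC arm can contain patients who never have the procedure, and a randomised control arm can contain patients who later do. Both remain in their arm when QALYs are compared as randomised. The claims groups contain neither kind of patient: everyone in the LAAC group has a coded procedure and no control does. The numerator would then describe receiving LAAC, and the denominator being assigned to it.

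The ICER is the outcome of module B2 and is meant to inform SHI providers and policymakers. A ratio whose two parts answer different questions corresponds to neither strategy. Its absolute size would be too large to the extent that non-receipt and crossover occur.

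**Working it through.** **1. Group definitions side by side**

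| Element | Trial QALYs (B1) | Claims costs (A2, SHI part) |
|---|---|---|
| LAAC group | Study arm (1.1, 1.2, Table 2) | LAAC coded by DRG and OPS (2.3.1) |
| Control group | Study arm; antiplatelet or no therapy possible (1.1, 2.2.1) | No LAAC documented, and on a NOAC or VKA (2.3.1) |
| LAAC-arm patient without procedure | Stays in the LAAC group | Cannot be in the LAAC group |
| Control who receives LAAC | Stays in the control group | Cannot be in the control group |

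**2. Does another section align them?**

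- Matching (2.4.2) uses age, gender, comorbidity, the two risk scores and control-group medication. None of these separates assignment from receipt.
- The sensitivity analyses (2.5) cover parameter uncertainty, the discount rate, linearity of quality of life between visits, sample selection and technical progress. They do not cover non-receipt or crossover.
- The limitations (section 3) mention differing variable definitions only in general terms.

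**3. Size**

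The article states no figure on this point, so there is none to reproduce. Its sample size (264, or 294 after loss to follow-up) is not affected.

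Let p be the share of the LAAC arm without LAAC and c the share of controls with LAAC. Let T and U be the mean QALYs with and without LAAC. Assume that effects are proportional to receipt.

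- LAAC arm as randomised: (1-p)T + pU
- Control arm as randomised: cT + (1-c)U
- Difference: (1-p-c)(T-U)

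The claims cost difference, D, is not diluted.

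- Mixed ICER: D / [(1-p-c)(T-U)]
- ICER with both parts by receipt: D / (T-U)
- Ratio of the two: 1/(1-p-c)

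If costs are also proportional to receipt, both parts as randomised give (1-p-c)D / [(1-p-c)(T-U)] = D/(T-U). The mixed ratio is therefore inflated against either consistent version.

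| p (assumed) | c (assumed) | 1-p-c | Factor |
|---|---|---|---|
| 0 | 0 | 1.00 | 1.00 |
| 0.03 | 0 | 0.97 | 1.03 |
| 0.05 | 0.05 | 0.90 | 1.11 |
| 0.10 | 0.10 | 0.80 | 1.25 |
| 0.15 | 0.10 | 0.75 | 1.33 |

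**The case against.** **No analysis set is named.** The article does not say that B1 is analysed by intention to treat; that could stand in a full protocol or SAP that is not shown. This stands. A reader might infer that the plan expressly divides an as-treated cost difference by an as-randomised QALY difference. The text supports this only as the natural reading of study arms in a randomised trial.

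**Claims data carry no assignment.** A procedure-based definition is unavoidable, and Table 2 concedes that it only approximates the trial. This also stands. The weakness lies in combining the two contrasts without alignment, not in the coding.

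**The split is not clean.** FIMA costs follow trial arm, which matters most for the societal perspective. In the lifetime model, transition probabilities are tuned in the claims groups, so the effect side is partly procedure-defined as well. The factor above should not be carried over to the lifetime ICER.

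**The index date.** A reader might infer from section 2.4.2, which compares costs before and after the quarter of LAAC, that LAAC-arm patients without a procedure have no start date. The documents do not support this. That sentence covers five years and works in quarters, which fits the claims cohort, where every LAAC patient has such a quarter. Trial data already run from baseline (2.2.3), with follow-up of up to 24 months.

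**Decision value.** A positive factor cannot change the ICER's sign. The Discussion contemplates dominance, where the size of the ratio matters little. This limits the consequence but does not remove it, since dominance is a possibility and not a result.

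**Conclusion.** The point holds in a limited form. On the natural reading, followed as written, the two- and five-year ICER mixes a cost contrast by receipt with a QALY contrast by assignment, and no stated matching step or sensitivity analysis corrects this. It is clearest for the SHI perspective.

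The direction is inflation of the ICER's absolute size whenever there is non-receipt or crossover and effects are proportional to receipt. The size cannot be derived from the documents: the factors of 1.00 to 1.33 rest on assumed rates, and at full adherence there is no distortion. The table should not be read as showing that this ICER is wrong by any particular percentage. The point is worth correcting before analysis, but it does not invalidate the design.

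**What to change.** 1. State in 2.4.3 that B1 compares QALYs as randomised.
2. In 2.4.2 and 2.4.4, put the SHI cost difference on the same contrast. For each trial arm, weight the SHI costs with and without LAAC by the share of that arm observed to receive LAAC.
3. Count attempted procedures as incurring procedure cost, even where no device is placed.
4. Vary the cost assigned to patients without LAAC. They cannot all be priced as SHI controls, because those controls are on a NOAC or VKA while trial patients may be on antiplatelet therapy or none.
5. Enter the receipt shares in the probabilistic sensitivity analysis (2.5).
6. Report alongside it an ICER with QALYs and costs both by treatment received.

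The cost is low. Section 2.1 already plans to use the trial's treatment arm, medication and periprocedural data. The price is a few more uncertain parameters. The treatment-received ICER also loses the protection of randomisation, so it should remain secondary.
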